### Data collection and follow-up

Figure 2 illustrates the process of the entire study. Clinical information will be collected prior to the initiation of CRRT. This includes gender, age, weight, baseline blood urea nitrogen, serum creatinine, urine output, comorbidities, Acute Physiology and Chronic Health Evaluation (APACHE)-II scores, Sequential Organ Failure Assessment (SOFA) score, hemoglobin, platelets, serum total calcium, and ionized calcium. Renal function will be classified according to KDIGO criteria [2].

**Figure 2. F0002:**
[figure not shown]
Flowchart of the study. CRRT: continuous renal replacement therapy; CVVHD: continuous veno-venous hemodialysis; CVVH: continuous veno-venous hemofiltration;

Pre-filter iCa, post-filter iCa, systemic total calcium, ionized calcium, and effluent total calcium will be measured two hours after the start of CRRT for each new circuit. The sites of blood sample collection are shown in Figure 3. The measurements will be performed using an arterial blood gas analyzer for serum ionized calcium, post-filter iCa, and pre-filter iCa. Blood samples will be sent to the central laboratory to measure systemic total calcium. Effluent total calcium will be measured by inductively coupled plasma emission spectrometry.

**Figure 3. F0003:**
[figure not shown]
Blood sample collection sites at various locations during continuous renal replacement therapy. ①: pre-filter iCa ②: post-filter iCa ③: systemic total and ionized calcium ④: effluent total calcium PBP: pre-blood pump; iCa: Ionized calcium

Electrolytes, arterial blood gas analysis, hourly citrate dose, and total citrate dose will be recorded every 6 h until the end of CRRT. The concentration of the 4% sodium citrate solution is 136 mmol/L, and the screening factor for citrate is 1.0. Therefore, the average citrate dose entering the patient’s body per hour will be calculated as follows: average citrate dose = 136 mmol/L * citrate infusion rate (L/h) * (1 - ultrafiltration rate/plasma flow). The total citrate dose will be calculated as follows: total citrate = hourly citrate dose * total treatment time.

At the end of CRRT, filter and venous pot clotting and individual filter lifetime will be recorded. Filter lifetime is defined as the time (in hours) from the start of CRRT to clotting or the end of the procedure. All data will be prospectively collected by physicians who are not involved in patient care.

To control for potential confounding factors from blood products containing citrate, the following measures will be implemented: 1) Blood products will only be administered when clinically necessary. 2) The timing and volume of all blood product administrations will be carefully documented. 3) Additional post-filter iCa levels will be measured at 2 and 4 h after any blood product administration. 4) These events will be recorded as potential confounding factors and will be considered in the final analysis.

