### CRRT parameter setting and management

PrismaFlex (Baxter Investment Co., Ltd, Chicago, IL) CRRT device and AN69 ST150 hemofilters (Baxter Investment Co., Ltd, Shanghai, China) will be used. Vascular access will be established by inserting a double-lumen catheter (SCW Medication Ltd, certification number: 20173664588, 12 Fr, 20 cm) into either the femoral or internal jugular vein. CRRT will be ended for any of the following reasons: achievement of therapeutic goals; coagulation of the filter; transmembrane pressure continuously > 250 mmHg; or continuous treatment for 48 h (to replace pipeline and filter).

This study is a before-after design in the same patient; each patient will receive both continuous veno-venous hemofiltration (CVVH) and continuous veno-venous hemodialysis (CVVHD) at least once. Patients will be initially randomized into either the CVVHD or CVVH groups and then crossed over to the other group during the second CRRT session. Regardless of whether CVVH or CVVHD is used, the initial settings will be as follows: blood flow rate of 150 ml/min, 4% sodium citrate flow rate of 230 ml/h, 10% calcium gluconate infusion rate of 10 ml/h, and a 5% sodium bicarbonate infusion rate (ml/h) of dialysate/replacement fluid × 0.0625 − 120. The therapeutic dose will be 30 ml/kg/h depending on the mode investigated, that is, a dialysate rate (ml/h) of 30 ml × body weight (kg) in the setting of CVVHD; on the other hand, the replacement fluid rate (ml/h) will be 30 ml × body weight (kg) in the setting of CVVH.

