The clinician will assess whether to adjust the CRRT parameters based on arterial blood gas and post-filter iCa concentration two hours after the start of CRRT. No adjustment of the citrate dose is required, and post-filter iCa levels will be monitored every four to six hours if the therapeutic goal of anticoagulation is achieved (post-filter iCa concentration 0.20–0.4 mmol/L). If anticoagulation is not achieved, the citrate infusion rate will be adjusted according to Table 1, and post-filter iCa levels will be monitored every two hours until the therapeutic goal is achieved. The goal of systemic iCa will be between 1.00 and 1.20 mmol/L. The 10% calcium gluconate infusion rate will not be adjusted, and arterial blood gas will be monitored every four to six hours if serum iCa concentration reaches the target. The calcium gluconate infusion rate will be adjusted according to Table 2, and arterial blood gas will be monitored every two hours until the target is reached if serum iCa concentration does not reach the target.

**Table 1. t0001:** Adjustment of 4% sodium citrate infusion rate according to post-filter ionized calcium level.

Post-filter iCa (mmol/L)	Change in citrate infusion rate
<0.2	20ml/h ↓
0.2–0.4	No change
0.41–0.45	10ml/h ↑
>0.45	20ml/h ↑

**Table 2. t0002:** Adjustment of calcium gluconate infusion rate according to systemic ionized calcium level.

Systemic ionized Ca^2+^ (mmol/L)	Change in 10% calcium gluconate infusion rate
>1.35	5ml/h ↓
1.2–1.35	2ml/h ↓
1.0–1.2	No change
0.91–0.99	2ml/h ↑
0.86–0.90	5ml/h ↑
0.75–0.85	7.5 ml/h ↑
<0.75	10ml/h ↑

If circuit clotting is detected, the circuit will be discontinued immediately to ensure patient safety. All clotting events will be documented in detail, including the time of detection, last recorded post-filter iCa level, circuit running time before clotting, and citrate dose at the time of clotting. The attending physician will then evaluate the patient’s clinical condition to determine whether immediate CRRT re-initiation is necessary or if CRRT can be temporarily discontinued until the next scheduled treatment. If clinical assessment indicates the need for immediate CRRT continuation, a new circuit will be initiated following the standard protocol. Given the short half-life of citrate, the time required for circuit replacement is believed to be sufficient to eliminate any carry-over effects.

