### Study objectives

The primary objective is to evaluate trends in post-filter iCa2+, pre-filter iCa effluent iCa2+ and total calcium, systemic iCa2+, and total calcium concentration over time in different RCA-CRRT modes.

The secondary objectives are to analyze the amount of citrate used in different modes to achieve the desired anticoagulant effect in current clinical practice, and to assess the incidence of new-onset metabolic complications (hypercalcemia, hypocalcemia, metabolic acidosis, metabolic alkalosis, citrate accumulation, hypernatremia, hyponatremia). The incidence of metabolic complications will be calculated as the number of new-onset metabolic complication events per 100 CRRT days. In this study, citrate accumulation is defined as the presence of a total serum calcium/ionized calcium ratio > 2.5.

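### After the 2 h adjustment, systemic iCa is steered to one target in both modes, but the calcium gluconate dose that absorbs a mode effect is neither a listed data item nor an objective

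*Protocol article*

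**What the plan says.** All places are in the protocol article.

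- **Common start.** *CRRT parameter setting and management*: "Regardless of whether CVVH or CVVHD is used, the initial settings will be as follows", and these settings include a "10% calcium gluconate infusion rate of 10 ml/h".
- **Common target and rule.** Same section: "The goal of systemic iCa will be between 1.00 and 1.20 mmol/L". Off target, "The calcium gluconate infusion rate will be adjusted according to Table 2". Table 2 has no mode-specific rows.
- **First decision at 2 h.** Same section: "The clinician will assess whether to adjust the CRRT parameters based on arterial blood gas and post-filter iCa concentration two hours after the start of" treatment.
- **What is compared.** The *Abstract* (Methods) makes the iCa difference at each site over time the primary outcome. *Study objectives* puts systemic iCa and total calcium over time in the primary objective. The *Introduction* allows that the modes might differ even in systemic calcium.
- **What is measured at 2 h.** *Data collection and follow-up* lists pre- and post-filter iCa and systemic total and ionized calcium, and "effluent total calcium will be measured two hours after the start of CRRT for each new circuit".
- **What is recorded afterwards.** Same section: "Electrolytes, arterial blood gas analysis, hourly citrate dose, and total citrate dose will be recorded every 6 h until the end of CRRT".
- **Dose outcome.** The only dose among the objectives is citrate: the aim is to "analyze the amount of citrate used in different modes to achieve the desired anticoagulant effect".

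Calcium gluconate appears only as a treatment setting, in the sections on solution preparation and CRRT parameters.

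**The concern.** Systemic iCa after 2 h is a feedback-controlled quantity. If one mode removes more calcium or returns less, staff following Table 2 raise the infusion until the reading is back on target. The effect then appears as a higher calcium gluconate dose rather than a lower iCa.

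The plan handles the same problem well on the circuit side. Post-filter iCa is titrated through citrate, so the citrate dose is recorded and compared. On the patient side the controlled level is compared without the dose that controls it.

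At stake is how the systemic part of the primary comparison is read. Near-equal later values are what the protocol tries to produce, so they say little about whether the modes differ in their effect on systemic calcium.

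**Working it through.** **1. The plan's own figures.** The article gives no expected mode effect, SD or baseline for systemic calcium. Its sample size concerns post-filter iCa only: 0.44 − 0.305 = 0.135 mmol/L, SD 0.2. With the SD read as that of the paired difference and a two-sided alpha of 0.05, power is 0.899 at n = 25 and 0.911 at n = 26. The stated 26 is reproduced, and this point does not depend on it.

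**2. The two titrated infusions side by side.**

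| | Circuit | Patient |
|---|---|---|
| Controlled level | post-filter iCa, 0.20–0.40 mmol/L | systemic iCa, 1.00–1.20 mmol/L |
| Titrated infusion | citrate (Table 1) | calcium gluconate (Table 2) |
| Level compared between modes | yes | yes |
| Dose a listed data item | yes, hourly and total | no |
| Dose an objective | yes | no |

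Table 2 steps are 2 to 10 ml/h. Against the 10 ml/h start that is 2/10 = 20% to 10/10 = 100%, so the infusion can move far enough to offset an effect.

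**3. Why the level alone is not enough.** Let *s* be the mode shift in systemic iCa at equal infusion rates, *k* the response of iCa per ml/h of calcium gluconate, and Δr the rate difference between modes. Near steady state the observed difference is

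D ≈ s + k·Δr.

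Table 2 drives Δr to the opposite sign of *s*, so D is smaller than *s*. Without Δr, *s* cannot be recovered from D.

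**4. Illustrative size.** Every input here is an assumption, except the Table 2 steps, the 10 ml/h start and the 2 h first decision: baseline iCa 1.08 (SD 0.06), *k* 0.02 or 0.04 mmol/L per ml/h, time constant 2 or 6 h, checks every 2 h off target and every 6 h on target.

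| s (mmol/L) | D at 2 h | D at 48 h | Rate difference at 48 h (ml/h, absolute) |
|---|---|---|---|
| 0.1 | 0.028–0.064 | 0.030–0.052 | 1.7–2.6 |
| 0.2 | 0.057–0.127 | 0.005–0.064 | 4.2–7.4 |
| 0.3 | 0.085–0.190 | −0.020 to 0.102 | 6.9–10.1 |

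Check against step 3, for s = 0.2, k = 0.02 and Δr = −6.787: 0.2 − 0.02 × 6.787 = 0.064, as simulated. For s = 0.2, 0.005/0.2 = 2.5% to 0.064/0.2 = 32% of the shift remains at 48 h. At 2 h, 0.057/0.2 = 28% to 0.127/0.2 = 64% is visible.

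**5. Sensitivity to baseline.** A second set of assumptions used an instant response, *k* 0.015–0.03, patient SD 0.08, reading SD 0.03 and 12–24 h of treatment. With the modes centred at mid-target (1.10), a 0.10 shift left about 0.03–0.06 mmol/L and a 0.20 shift about 0.06–0.11. With the modes straddling 1.00, a 0.10 shift left 0.021–0.038 at 12 h. The no-change band is 0.20 mmol/L wide, so patients who start mid-band are often not titrated and keep their difference.

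**6. When control fails.** With s = 0.4 and k = 0.02, about 0.19 mmol/L remained at 48 h because the infusion had reached zero.

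**The case against.** **The 2 h sample precedes titration.** Both modes run at 10 ml/h until the first planned decision, and systemic total calcium, systemic iCa and effluent total calcium are all measured then. This stands. A reader might infer that the plan cannot see any mode effect on systemic calcium, and the documents do not support that. However, 2 h may be short of steady state: under the slow response above, a 0.1 shift showed as only 0.028 mmol/L at 2 h. Nor does one early sample answer a question posed over time.

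**Systemic iCa is not the only patient-side measure.** Systemic total calcium, effluent calcium and the incidence of hypo- and hypercalcemia are also objectives. This stands too, and it would be wrong to say that only the controlled level is compared. These measures help in part: total calcium also depends on what is infused, effluent total calcium is scheduled once per circuit at 2 h, and titration itself reduces calcium events.

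**The article is condensed.** The case report forms are not shown, and charts may well hold the pump rate. That weakens the statement that the rate is unrecorded, which is why it is put here as not being a listed item. It does not supply a comparison: the objectives are stated explicitly, and calcium dose is not among them.

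**The aim is post-filter iCa.** True, and the hypothesis on dose concerns citrate. But systemic calcium over time was placed in the primary objective, so its interpretation matters. No passage says that similar systemic values will be reported as no effect; that is a risk of misreading, not a stated intention.

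**Conclusion.** The point holds for systemic calcium after the first adjustment decision at 2 h. If the protocol is followed, the later between-mode difference in systemic iCa is biased toward zero, and the calcium gluconate dose that carries the displaced part is neither a listed data item nor an objective.

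The direction follows from Table 2 and the common target. The size does not follow from the documents. Across the assumptions tried, a 0.20 mmol/L shift left between 0.005 and about 0.11 mmol/L. That range depends on the baseline iCa, the response per ml/h and the treatment time, so it should not be quoted as a property of this trial.

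A reader might also infer that the main result is undermined. It is not: the post-filter iCa hypothesis and the sample size built on it are untouched. This is a worthwhile correction to how one part of the primary comparison is captured and read, not a fatal flaw.

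**What to change.** 1. Record the calcium gluconate rate at the start and at each change, with the time.
2. Add the time-averaged calcium gluconate dose per session, from 2 h to session end, as a secondary outcome beside citrate dose, compared within patient between modes. A time average copes with sessions of unequal length.
3. Name the 2 h systemic calcium comparison as the one made before titration, at equal infusion rates.
4. State that systemic calcium after 2 h will be interpreted only together with the calcium dose. Entering the rate as an ordinary covariate is no substitute, because the rate responds to the iCa readings being modelled.

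The cost is one case-report-form field for a pump rate that staff already set, and one more secondary comparison. There is no new sample or procedure, and no dose, target or adjustment rule changes. The field should be in place prospectively, since the rates may not be recoverable later.

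### Read literally, the formula for citrate entering the patient leaves out diffusive removal, so equal infusions give a higher calculated dose in CVVHD than in CVVH

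*Protocol article*

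**What the plan says.** Under Data collection and follow-up, the article introduces its calculation with "the average citrate dose entering the patient’s body per hour will be calculated as follows" and gives one expression for both modes: "average citrate dose = 136 mmol/L * citrate infusion rate (L/h) * (1 - ultrafiltration rate/plasma flow"). The stated basis is that "the screening factor for citrate is 1.0". A cumulative figure is then built on it: "total citrate = hourly citrate dose * total treatment time".

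CRRT parameter setting and management starts both modes at the same settings, including "blood flow rate of 150 ml/min" and "4% sodium citrate flow rate of 230 ml/h". The treatment dose is "a dialysate rate (ml/h) of 30 ml × body weight (kg) in the setting of CVVHD"; in CVVH the same volume is replacement fluid.

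Study objectives includes the secondary aim to "analyze the amount of citrate used in different modes to achieve the desired anticoagulant effect". The Introduction hypothesises that a dialysis-based mode raises citrate requirements. The limitations state that plasma citrate is not measured.

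**The concern.** The trial rests on the difference between convection and diffusion, and the Introduction itself attributes solute transport in hemodialysis to a concentration gradient. The citrate formula has only a convective term. In CVVH the replacement fluid is taken off again as ultrafiltrate, so citrate removal is counted. In CVVHD, on the ordinary meaning of ultrafiltration, only net fluid removal is counted, and the article gives no value for that. Citrate leaving in the dialysate is not subtracted.

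Two sessions with the same infusion would therefore receive different calculated doses, and the difference lies in the hypothesised direction. With no citrate measurement, the study has no direct check on the calculated load.

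The formula also estimates net load reaching the patient, whereas the objective speaks of citrate used to achieve anticoagulation, which is naturally the infused amount. The article leaves open which of the two will be compared.

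**Working it through.** The article reports no result from the formula, so there is no figure to reproduce. The check applies the formula as written to the initial settings.

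**Inputs from the article:** citrate solution 136 mmol/L; citrate rate 0.230 L/h; blood flow 150 ml/min = 9.0 L/h; treatment dose 30 ml/kg/h; sieving coefficient 1.0.

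**Assumptions not in the article:** weight 70 kg (range 50-80); haematocrit 0.30 (range 0.25-0.35); net fluid removal zero; plasma flow = blood flow × (1 − haematocrit), with no predilution.

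**Step 1, infused citrate, either mode:** 136 × 0.230 = 31.28 mmol/h.

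**Step 2, formula as written, 70 kg:** plasma flow = 9.0 × 0.70 = 6.3 L/h; treatment volume = 0.030 × 70 = 2.1 L/h.

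- CVVH: 31.28 × (1 − 2.1/6.3) = 20.85 mmol/h.
- CVVHD: 31.28 × (1 − 0/6.3) = 31.28 mmol/h.
- Difference 10.43 mmol/h; ratio 1.50. Over 48 h: 10.43 × 48 ≈ 500 mmol.

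For scale, a 20 ml/h step in Table 1 is 136 × 0.020 = 2.72 mmol/h, so the gap equals nearly four such steps (10.43/2.72 = 3.8). For the formula to return the same dose as CVVHD at 230 ml/h, the CVVH infusion would have to be 230/(1 − 2.1/6.3) = 345 ml/h.

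**Step 3, range of the ratio, 1/(1 − treatment volume/plasma flow):**

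- 50 kg, haematocrit 0.25: 1/(1 − 1.5/6.75) = 1.29.
- 80 kg, haematocrit 0.35: 1/(1 − 2.4/5.85) = 1.70.

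Net fluid removal of 0.2 L/h in both modes (70 kg, haematocrit 0.30) gives 30.29 against 19.86 mmol/h, ratio 1.52. Counting the citrate volume as ultrafiltrate in both modes gives 1.53. The direction does not change.

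**Step 4, effluent in place of ultrafiltration, 70 kg, haematocrit 0.30:** CVVHD load = 31.28 × (1 − s × 2.1/6.3), where s is the dialysate saturation for citrate.

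| s | CVVHD, mmol/h | Ratio to CVVH (20.85) |
|---|---|---|
| 1.0 | 20.85 | 1.00 |
| 0.9 | 21.90 | 1.05 |
| 0.8 | 22.94 | 1.10 |
| 0.7 | 23.98 | 1.15 |

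Most of the 50% excess disappears.

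**Step 5, dilution in CVVH:** the article does not say whether replacement fluid enters before or after the filter. If all of it entered before, the fraction removed would be 2.1/(6.3 + 2.1) = 0.25 and the CVVH load 31.28 × 0.75 = 23.46 mmol/h. CVVHD at s = 1.0 would then be 20.85/23.46 = 0.89 of CVVH. The true net-load comparison therefore depends on this choice as well.

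**Step 6, the total:** for the same infusion of 31.28 mmol/h, 24 h gives 751 mmol and 48 h gives 1,501 mmol infused. These run times are illustrative; the article gives only the 48 h maximum. Runs may also end at clotting, high transmembrane pressure or the therapeutic goal, so the total mixes citrate need with circuit survival.

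**The case against.** The strongest objection is that ultrafiltration rate is not defined for either mode. If the investigators mean total effluent, the bias largely disappears (ratio 1.00 at full saturation), and a fuller protocol may say so. This stands as a limit: the bias belongs to the literal reading. It does not remove the point. The same section uses effluent as a separate term, and the formula is derived from a sieving coefficient, which describes convection.

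A second objection also stands. A reader might infer that the secondary endpoint is bound to show more citrate in CVVHD. The article does not support that. It nowhere names the formula's output as the comparison variable for citrate used, and the raw infusion rate is free of this bias.

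Third, a reader might count the run-length dependence of the total as more bias in the same direction. It is a separate matter and could act the other way. On the trial's own reasoning, dialysis may weaken anticoagulation; if that shortened CVVHD runs, total citrate in CVVHD would fall. The hourly dose is also recorded, so a measure not multiplied by run time already exists.

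Finally, the primary calcium outcomes and the citrate-accumulation definition (total to ionized calcium ratio) do not use the formula.

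**Conclusion.** The concern holds in a conditional form. On the literal reading, the stated formula gives a calculated dose about 50% higher in CVVHD at identical infusion (70 kg, haematocrit 0.30, no net fluid removal, no predilution), and 29-70% higher over 50-80 kg and haematocrit 0.25-0.35. The size depends on those assumed values; the direction does not. If this dose or the derived total serves the secondary citrate objective, the comparison is biased towards the hypothesis.

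This is a stated rule that treats the two modes unequally, so it is more than a detail left to the analysis plan. It does not threaten the primary comparison, and the documents do not establish that the secondary result will be wrong.

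**What to change.** 1. Define citrate use as the infused amount: 136 mmol/L × actual infusion rate, as a time-weighted mean in mmol/h. Name this as the measure for the secondary objective. Do not use the total over the run as the between-mode comparison.
2. Report net patient load separately under its own name. Replace ultrafiltration rate by total effluent rate: ultrafiltrate in CVVH, dialysate plus net ultrafiltrate in CVVHD. State the citrate saturation coefficient assumed for dialysis, with a sensitivity range such as 0.8-1.0, and state whether the CVVH calculation assumes pre- or post-filter replacement.
3. Confirm that actual dialysate and ultrafiltration rates are recorded. The formula implies that infusion and ultrafiltration rates are available, but the article's list of recorded items does not include dialysate rate.

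The cost is a change of analysis wording, plus recording the rates if they are not already captured. Treatment is unchanged. The small downside is that net load then rests on explicit saturation and dilution assumptions; the infused amount needs neither.

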### Statistical analysis

Data will be analyzed using SPSS 23.0 statistical software (IBM Co., NY). Continuous variables will be presented as means and standard deviations (for normal distribution) or medians and interquartile ranges (for non-normal distribution). A paired *t*-test will be used for normally distributed variables, and the Wilcoxon signed-rank test will be used for non-normally distributed variables. Categorical variables will be presented as numbers and percentages and analyzed using the *χ*^2^-test or Fisher’s exact tests, as appropriate. For the crossover design, we will specifically examine both carry-over and period effects. The carry-over effect will be assessed by comparing the sum of the outcomes between sequences using a t-test or Mann-Whitney U test depending on data distribution. The sequence of interventions will be randomly assigned to minimize potential period effects. A two-sided *p* < 0.05 will be considered a statistically significant difference.

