## Discussion

Post-filter iCa level is crucial for adjusting the citrate dose during RCA-CRRT. However, there is a lack of clinical data demonstrating the effects of different CRRT modes on ionized and total serum calcium levels in patients receiving RCA-CRRT with a calcium-containing replacement solution. We hypothesize that post-filter iCa concentration is higher in CVVHD than in CVVH under RCA-CRRT using a calcium-containing replacement solution. If this hypothesis is true, patients may require a higher citrate dose, thereby increasing the risk of citrate-related adverse effects. This study will expand previous work and provide new data regarding the impact of different RCA-CRRT modes on iCa, citrate dose, and citrate-related adverse effects.

While directly measuring citrate and calcium concentrations in the ultrafiltrate would provide a more controlled assessment of solute removal across different CRRT modes, our study aims to evaluate the clinical implications of citrate removal in actual patient care settings. The patient-based approach allows us to observe how variations in citrate removal affect circuit survival and safety parameters under real clinical conditions, including the influence of individual patient factors. This design better reflects the practical challenges and outcomes in routine clinical practice, though we acknowledge it introduces more variability in our measurements. The trade-off between controlled laboratory conditions and clinical relevance was carefully considered in our study design, and we chose to prioritize clinical applicability of our findings.

The iCa levels can be influenced by multiple factors including blood pH, acid-base status, and phosphate levels. To consider these potential confounding factors, we will collect comprehensive blood gas analysis data and biochemical parameters throughout the CRRT sessions. The crossover design of our study will help minimize between-subject variations, as each patient will serve as their own control. Furthermore, we will include these parameters as covariates in our statistical analysis to adjust for their potential effects on iCa levels. This comprehensive analytical approach will strengthen the reliability of our conclusions despite the complex nature of factors affecting iCa homeostasis.

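### Filter lifetime merges clotted filters with filters still patent at a goal-reached or 48-h stop, and the named tests would treat every duration as complete

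*Protocol article*

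**What the plan says.** All places are in the protocol article.

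- **Definition** (Data collection and follow-up, after Figure 3): "Filter lifetime is defined as the time (in hours) from the start of CRRT to clotting or the end of the procedure". The sentence before it reads: "At the end of CRRT, filter and venous pot clotting and individual filter lifetime will be recorded".
- **How a session can end** (CRRT parameter setting and management): "CRRT will be ended for any of the following reasons: achievement of therapeutic goals; coagulation of the filter; transmembrane pressure continuously > 250 mmHg". The fourth reason in that list is a time limit: at 48 h the circuit is changed.
- **What is recorded at clotting** (same section, after Table 2): "All clotting events will be documented in detail, including the time of detection, last recorded post-filter iCa level, circuit running time before clotting".
- **Tests** (Statistical analysis): for continuous variables, a paired t-test if normally distributed; otherwise "the Wilcoxon signed-rank test will be used for non-normally distributed variables". No time-to-event method and no censoring rule is named.
- **Stated interest** (Discussion): the patient-based approach is said to let the investigators "observe how variations in citrate removal affect circuit survival and safety parameters under real clinical conditions".
- **Objectives** (Study objectives): calcium concentrations over time are primary; citrate amount and metabolic complications are secondary. Filter lifetime and circuit survival are not listed.

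**The concern.** Two of the four listed reasons for ending a session, goal achievement and the 48-h limit, say nothing about the filter having failed. For such a session the time to clotting is known only to exceed the recorded duration, so it is a censored time. The definition gives it the same standing as a duration that ended in clotting, and a paired t or signed-rank test has no means of telling them apart.

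If the modes are compared on this variable, two things can happen:

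- **Dilution.** When elective stops are frequent, many durations reflect when treatment was no longer needed, and a real difference in clotting shrinks.
- **A false difference.** If elective stopping is faster under one mode, recorded lifetime differs even where clotting does not.

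At stake is what the study can say about circuit survival, which the Discussion offers as one reason for working in patients and not under laboratory conditions.

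**Working it through.** **The article's own figure.** The only computed figure is the sample size of 26, for post-filter ionized calcium. The difference is 0.44 − 0.305 = 0.135 mmol/L, with two-sided α = 0.05 and power 0.90. Taking 0.2 as the SD of the within-patient difference, the normal approximation gives ((1.960 + 1.282) × 0.2 / 0.135)² ≈ 23.06, so 24. The noncentral t gives power 0.899 at n = 25 and 0.911 at n = 26. The stated 26 reproduces and does not depend on filter lifetime, which has no planned size or power.

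**Inputs for the illustration.** From the article: the 48-h limit, the list of stop reasons, and 30 patients each receiving both modes. Assumed, because the article gives no rates: exponential times, median time to clotting 60 h (30 h for a doubled hazard), and median time to an elective stop from 12 h to none.

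**Formulas.** Let h be the clotting hazard and g the elective-stop hazard, each ln 2 / median.

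- Mean recorded lifetime = (1 − exp(−48(h + g))) / (h + g)
- Share of sessions ending in clotting = h / (h + g) × (1 − exp(−48(h + g)))

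Example, clotting median 60 h and elective median 24 h: h = 0.01155, g = 0.02888, sum 0.04043. Mean = (1 − exp(−1.941)) / 0.04043 = 0.8564 / 0.04043 = 21.2 h. Share clotted = 0.01155 / 0.04043 × 0.8564 = 0.245.

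| Median elective stop, both modes | Mean lifetime, clotting median 60 h | Mean lifetime, clotting median 30 h | Difference |
|---|---|---|---|
| none (48-h limit only) | 36.8 h | 29.0 h | 7.8 h |
| 48 h | 27.4 h | 22.2 h | 5.2 h |
| 24 h | 21.2 h | 17.7 h | 3.5 h |
| 12 h | 13.9 h | 12.1 h | 1.8 h |

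The clotting difference is the same in every row; only elective stopping changes. Reading down the second column, recorded lifetime at identical clotting runs from 36.8 h to 13.9 h. Time to clotting restricted to 48 h stays at 36.8 h throughout.

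**Unequal stopping, equal clotting.** With clotting median 60 h in both modes and elective medians of 48 h v 24 h, mean recorded lifetime is 27.4 h v 21.2 h, a 6.2 h difference with no difference in clotting.

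**Simulation.** 30 pairs, 1,500 runs, sessions generated independently. Wilcoxon signed-rank on recorded lifetime is set against a log-rank test with non-clotting ends censored. Entries are the proportion with p < 0.05.

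| Scenario | Wilcoxon | Censored log-rank |
|---|---|---|
| Equal clotting, elective 48 h in both | 5% | 6% |
| Equal clotting, elective 48 h v 24 h | 27% | 6% |
| Hazard ratio 2, no elective stops | 42% | 51% |
| Hazard ratio 2, elective 24 h in both | 14% | 33% |

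The signed-rank test keeps its level when stopping is alike in the two modes. It loses power when elective stops are frequent, and it loses its level when stopping differs by mode.

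**The case against.** The case on the other side is substantial, and most of it bears on weight and wording.

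- **The text does not call a non-clotting end a failure.** A reader might infer that elective and 48-h stops are counted as filter failures, so that modes are compared on session length instead of clotting. The article does not say this. The defined duration is the time variable a censored analysis needs, clotting is recorded alongside it, and the recorded lifetime is a mixture of the two. This stands.
- **No between-mode test of lifetime is stated.** Filter lifetime is a recorded item, not an objective, and the comparison is inferred from the general sentence on continuous variables and from the Discussion. An analysis plan that is not shown could set censoring rules. This stands as a limit, which is why the point is conditional. It does not remove the point, because the article itself fixes both the definition and the tests.
- **Shorter second sessions do not by themselves create a mode difference.** A reader might infer that they would. Mode order is randomized, so a pure period effect falls on both modes and largely balances.
- **The 48-h limit alone does no harm to the mean.** With no elective stops, 36.8 h v 29.0 h is the restricted mean time to clotting over 48 h, a legitimate quantity. Setting its 21% reduction beside the 50% reduction in median compares two different summaries and shows no bias.
- **Nothing in the article says stopping differs by mode.** Both modes use the same dose of 30 ml/kg/h. Bedside clinicians and nurses know the mode, so a difference is possible, but it remains an assumption.

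**Conclusion.** The point holds in a limited form and is minor. The definition merges clotted filters with filters still patent at a goal-reached or 48-h stop, and the only tests named for continuous variables treat every duration as complete. If circuit survival is compared between modes on that basis, the result mixes clotting with session length.

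Under the assumed rates, a doubled clotting hazard shows as 3.5 h instead of 7.8 h when elective stops have a median of 24 h in both modes, and power is about 14% against 33% for a censored test. A false difference (about 27% significant results) requires elective stopping to differ by mode. These sizes rest on exponential times, on stopping unrelated to clotting risk, and on rates the article does not give.

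The primary outcome, the listed secondary objectives and the sample size are unaffected. Nor does the article support the inference that clotting information is lost: clotting and its timing are captured. What it does not state is that the reason for every other stop is recorded.

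**What to change.** Leave the session-ending rules as they are and change only the definition and the analysis:

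1. Keep the recorded duration, and define the event as filter clotting.
2. Censor goal-reached, 48-h and other non-clotting ends.
3. State in advance how an end for transmembrane pressure is classified, as event or as censored.
4. Record the reason for every stop, not only for clotting.
5. Compare modes with a time-to-event method that respects the crossover: Cox regression stratified by patient or with a patient frailty, including period. Show Kaplan-Meier curves or clotting events per circuit-hour alongside. This replaces paired t or Wilcoxon on raw duration.

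The cost is one extra recorded field, a few lines of wording and slightly more analysis work. Clotting status and time are already collected. The choice should be fixed before the data are analyzed, so that the method is not chosen after the results are seen.
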